[figure not shown][figure not shown]

# Summary

## Study Objectives

We propose to develop a novel community-based intervention, using the “storytelling” method, to enhance the control of elevated blood pressure in adults residing in rural communities in the Red River Delta region of Vietnam and to evaluate the feasibility and acceptability of the intervention through the conduct of a cluster feasibility randomized trial.

## Study Design and Trial Outcomes

A cluster feasibility randomized trial will be conducted in Hung Yen province, Vietnam to evaluate the feasibility and acceptability of a novel community-based intervention using the “storytelling” method to enhance the control of HTN in adults residing in 4 rural communities.

Feasibility outcomes include recruitment, retention, engagement, and treatment fidelity. Exploratory outcomes will include levels of systolic and diastolic BP and the proportion of participants with controlled BP defined as in JNC-8 at three months after randomization.

## Trial Intervention

The intervention will center on stories about living with HTN, with patients speaking in their own words. The stories will be obtained from particularly eloquent patients, or “video stars” identified during Story Development Groups.

## Study Population

Four eligible communes in 4 districts in Hung Yen province will be randomly assigned to the intervention group (n=2) or comparison group (n=2). Within each selected commune, 25 individuals 50 years or older with HTN will be enrolled in the trial resulting in a total sample size of 100 patients. Each of the selected communes satisfy the following criteria: (1) have a community health center with a medical doctor; (2) are not currently participating in other studies for hypertension control; and (3) have a minimum geographic separation of 12 kilometers (7 miles) from all other study communes to minimize possible contamination.

## **Patient Population**

Individuals 50 years or older with uncontrolled HTN (n = 100) will be assigned to intervention versus comparison status based on the commune in which they reside.

## **Specific Aims**

The main goal of the “Storytelling” intervention will be to promote engagement in preventive health care and lifestyle behaviors and improve the expected low rates of hypertension (HTN) control among adult residents of a rural province in Vietnam. The specific aims of our work are to develop and evaluate the feasibility and acceptability of a novel community-based intervention using the “storytelling” method to enhance the control of HTN in middle-aged and older adults residing in a rural province of Vietnam which will be accomplished in several overlapping phases.

### Phase 1: Developmental Phase: Intervention development

Specific Aim 1: Engage community members from Hung Yen province, a rural province of Vietnam, to produce an interactive, multi-media intervention based on patients’ stories in culturally and literacy appropriate ways.

Specific Aim 2: Produce a series of interactive DVDs that encompass health message domains which are consistent with the Health Behavior Model, the Adapted Slater Model of Narrative Communication, the cultural background of participants, and the desired behavior change.

Specific Aim 3: Use state-of-the art approaches to culturally adapt and translate intervention and assessment methods that have been successfully used in other settings and for other populations.

### Phase 2: Implementation Phase: Feasibility trial

Specific Aim 4: Conduct a feasibility cluster-randomized controlled trial (RCT) with 4 communes randomly assigned to either an intervention or comparison condition. Feasibility

and acceptability outcomes will include participant engagement, recruitment, retention, intervention fidelity, feasibility of assessment procedures, and participant satisfaction.

## **Background and Rationale**

### **Epidemiologic Transition and Cardiovascular Disease (CVD)**

Vietnam is in an epidemiological transition. The overall morbidity and mortality from non-communicable diseases (NCDs) has been rising rapidly over the last two decades and is a major societal problem.[1] The changing profile of chronic disease in Vietnam parallels changes in the socio-demographic characteristics of the population and increases in life expectancy.[1-4] Increased life expectancy prolongs the life-course exposure to risk factors for cardiovascular disease (CVD), rendering the population more susceptible to diseases of the heart and circulation; CVD is now the leading cause of death in Vietnam, accounting for 25% of all deaths.[5] Concomitant with these trends, the major risk factors for CVD are either on the rise or at alarming levels in the general population. A national survey in eight Vietnamese provinces and cities found that the prevalence of hypertension (HTN) was 25% in persons 25 years and older, and it increased with advancing age (prevalence of HTN in persons 45-54 years and 55-64 years were 42% and 58%, respectively).[6] The Vietnam National Health Survey in 2002 estimated that, by 65 years of age, nearly one half of all Vietnamese men and women will have HTN.[7]

### **Hypertension and Its Impact**

The World Health Organization (WHO) considers HTN to be one of the most important causes of premature mortality worldwide.[8] It is also one of the most preventable CVD risk factors; it can be easily detected and effectively treated according to evidence-based guidelines with low-cost drugs.[9] [10] In spite of the economic hardships that exist in Vietnam, inexpensive health care including generic medications to treat HTN are readily available. Our research team has, however, reported disconcerting results from a population-based survey of residents of Thai Nguyen province in 2011 in which only one

third of persons diagnosed with HTN were aware of their condition. Furthermore, of those diagnosed with HTN, only 43% were on treatment, and of those being treated for HTN, only 39% had achieved appropriate control.[11] Furthermore, in a rural district in Vietnam, 83% of participants who had high blood pressure (BP) were not aware of their HTN, and only 6% of those with HTN were being treated.[10] These findings flow not only from inadequate training of community health care workers in effective health communication and lack of necessary skills to communicate the diagnosis of HTN, and the importance of control measures, to the patient, but also from poor knowledge of the importance and health impact of HTN in the general population. Indeed, a recent survey in Vietnam showed that 70% of community health workers were unable to identify essential questions to be asked of a patient with HTN.[12] Likewise, a nationwide survey in 2007 found that only 23% of participants understood what were the major risk factors for CVD with men and women from rural areas having particularly poor knowledge about these risk factors.[7] These findings suggest a clear need for educating the Vietnamese population, especially middle-aged and older adults residing in rural areas, about CVD risk factors, the adverse health effects of HTN, and the development of acceptable and sustainable low-cost interventions to effectively prevent and treat elevated BP.

### **Conceptual Models**

We urgently need novel, large-scale, and sustainable public-health interventions for detecting, treating, and controlling HTN in Vietnam. Narrative intervention, or “storytelling,” is a promising approach for engaging low-literacy populations in the treatment of their HTN. A previous randomized controlled trial of an interactive, multi-media storytelling intervention by our team documented a substantial benefit for BP control.[13] However, this work was carried out among inner-city African Americans in Birmingham, Alabama and some of the protocols used for this intervention may not directly apply to different settings. However, as storytelling is a central part of what makes us human, narrative interventions have the flexibility to undergo adaptation to achieve the best results in new cultural settings.

With this flexibility of design and approach, we are adapting our previous storytelling work for a rural Vietnam population. More specifically, we are seeking to develop a novel community-based intervention using the “storytelling” method to promote the control of HTN among middle-aged and older adults residing in rural communities in the Red River Delta region of Vietnam and to evaluate the feasibility and acceptability of the intervention with a feasibility cluster-randomized trial.

Described briefly, the intervention development process begins with Story Development Groups, consisting of small groups of patients who gather for a guided discussion. From these groups, particularly eloquent “video stars” are selected to tell their story, which may focus on the health consequences of uncontrolled HTN, overcoming barriers to HTN control, adherence to prescribed medication, and importance of dietary and lifestyle changes among other topics that connect the narrative directly with cultural practices that can have an effect in the control of HTN. The intervention team then develops customized interview guides, captures video footage, and packages the stories in an appropriate context along with supporting didactic material.

Storytelling is inherently culturally appropriate and well suited for populations across the literacy spectrum; it is especially well suited for populations with low health literacy.[14]

**Figure 1. Adapted Slater Model of Narrative Communication**

[figure not shown]

Conceptually, our intervention rests on two models to empower hypertensive patients with the support of community health workers: the Health Belief Model[15] and the adapted Slater Model of Narrative Communication Theory (Figure 1).[16]

The Health Belief Model includes four constructs representing the perceived threat and net benefits of treatment including perceived susceptibility, disease severity, benefits of treatment, and barriers. The model posits that a person is more likely to take action or change their behavior when the perceived severity and susceptibility of the disease are high

and the balance between perceived barriers to changing behavior or treatment and benefits is favorable. Because HTN is primarily an asymptomatic, chronic condition that leads to serious morbidity and mortality if left untreated over several years, strategies for improving the rates of HTN control in the general population must address falsely held patient beliefs.[17-19] Our pilot data from Vietnam demonstrates a compelling lack of such awareness, and our previous work with storytelling suggests that our storytelling approach is an effective strategy for overcoming these barriers in a low-literacy population.

Narrative communication appeals to the human affinity for “storytelling.” Its effectiveness in changing attitudes and behavior follows from the ability to break down cognitive resistance through transportation (absorption in the story line) and identification with characters in the narrative. Thus, the participant is transported into the world of the characters, in this case hypertensive individuals, and becomes absorbed in the narrative content, rather than focusing on the embedded subtext of behavior change.[20, 21] The conceptual basis for the influence of stories on behavior derives from personal relevance, increased risk perception, increased self-efficacy, and transportation into the narrative (Figure 1).

## **Trial design**

### **Study Setting**

**“We Talk About Our Hypertension”** will be conducted in the Red River Delta Region which is an agriculturally rich and densely populated area in northern Vietnam. In this region, communes in Hung Yen province were selected based on their general representativeness. Hung Yen province has a population of approximately 1.2 million, organized into 10 districts and 161 communes. In Vietnam, the health system is organized into four levels, namely central, provincial, district hospital, and the lowest level, which includes the community health centers (CHCs) that are responsible for providing primary health care and outpatient services. Patients with HTN are typically treated and managed at the CHCs unless they need to be referred for a higher level of care.

All communes in Hung Yen have adequate electricity. Data from a national survey in 2010 showed that 94% of households in Hung Yen province have a television, 43% of households have landline phones, and 37% of the population uses mobile phones.[22] Each participant will receive a DVD player, which will be used to view DVDs, at no cost and will be given assistance in setting it up and also provided with ongoing troubleshooting.

### **Phase 1. Intervention Development**

Intervention development will be based on successfully used protocols for story elicitation, review, editing, and packaging and tested in prior projects such as TRUST and Culturally Sensitive Intervention (CSI): Birmingham.[13] The intervention will center on stories about living with HTN, with patients speaking in their own words. The stories will be obtained from particularly eloquent patients, or “video stars,” identified during Story Development Groups. The power of this approach hinges on capturing authentic stories from real patients. In brief, the approach includes: (1) selection of “star” storytellers through Story Development Groups; (2) creation of a customized interview guide designed to elicit the most powerful stories for each star; (3) videotaping each star telling his or her story; (4) decomposition of videotaped interviews into “story units;” (5) rating of message strength for the story units by independent reviewers fluent in Vietnamese; (6) weaving the most highly rated video segments into a cohesive and authentic video production; and (7) piloting and “usability testing”[23] with multiple iterations and a “Thinking Aloud” Protocol.[24, 25]

The process will begin with six Story Development Groups to: (1) gather critical data to inform intervention content; (2) identify patients who will serve as our storytelling “stars”; and (3) develop customized interview guides for the subsequent videotaping of each star. Each Story Development Group will have between 6 and 8 participants with newly diagnosed or longstanding HTN. These HTN “stars” will have had positive experiences in controlling their HTN and be particularly eloquent and persuasive advocates.

**“We Talk About Our Hypertension”** will focus on how the stars in the videos manage their HTN using positive behaviors. Digital video sequences will be rated by

strength of content and emotional engagement according to our conceptual models based on adaptations of previously developed protocols from CSI: Birmingham.[13] The edited stories will be integrated into two interactive DVDs. Each DVD will have five stories on it and be about 30 minutes in length in total.

The content of the DVDs will focus on a series of health message domains which are consistent with the HBM, narrative communication, the cultural background of participants, and the desired behavior change. The domains are as follows: stories about the health consequences of HTN as a silent killer, overcoming barriers to HTN control, and importance of adherence to prescribed medication, quitting smoking, dietary changes, weight loss, reducing sodium/salt intake, increasing levels of physical activity, and moderate use of alcohol, patients' perceptions about the benefits of traditional medicine and Western medicine, and the use of traditional medicine in addition to Western medicine for managing HTN. Storytellers will discuss culturally and literacy specific aspects of patients' perceptions of HTN and HTN treatment and deal with the daily challenges presented by achieving HTN treatment goals within the broader context of the patient's life. In addition, the stories will be supplemented by more didactic "Learn More" content. The Learn More section will be coordinated with specific patient stories and will fill in gaps not covered by the storytellers. The Learn More section will include in lay language such topics as: What is HTN? What are the consequences of untreated HTN? How may HTN be treated without medications? What are some common medications used to treat HTN? How do these medications work and what are their side effects? Why is it important to take your medication even when you are feeling well? How should I speak to my doctor about high BP?

## **Phase 2. Randomized Trial Evaluating the Feasibility and Acceptability**

We will conduct a feasibility cluster RCT with 100 adult hypertensive participants from 4 communes (25 participants from each commune) in Hung Yen province to assess the feasibility and acceptability of both the intervention process and the process of randomization and evaluation.

## *Study Sites*

In consultation with the Chief Cabinet Officer of Hung Yen province, four communes in four separate districts with a total population of approximately 12,000 men and women have been selected for this feasibility study. With a national HTN prevalence rate among adults of about 25%, and over half of the total population being 25 years and older, the selected sites will provide enough persons with HTN for the proposed feasibility trial. Each of the selected communes have satisfied the following criteria: (1) having a CHC with a medical doctor; (2) not currently participating in other studies to improve CVD risk management; and (3) the distance between any 2 selected communes is more than 12 kilometers (7 miles) to minimize possible contamination.

## *Participant Eligibility*

To be enrolled in this feasibility study, consenting adult men and women must fulfill each of the following criteria: (1) be a resident of the selected commune; (2) be aged 50 years or older; (3) have a diagnosis of HTN according to the 7th Joint National Commission of High Blood Pressure (JNC 7)[9]; (4) have BP measures consistently elevated at 2 time points (screening and 2 week after screening); (5) not be cognitively impaired (as assessed by study physicians); (6) not be a “story teller” who was used to develop the intervention; and (7) not be a family member of another participant in the study. We will restrict our patient population to patients aged 50 years or older since their prevalence of HTN is greatest, they are interested in storytelling, and they face unique challenges to managing their HTN.

Trained study nurses at study sites will explain to eligible persons about the study’ procedures and will obtain informed consent. Patients will be excluded if they are pregnant or unable or unwilling to provide informed consent.

## *Study Recruitment and Randomization*

Four eligible communes will be randomly assigned to either the intervention or comparison condition. Participant assignment to respective study arms will be based on randomization status of their communes. This allocation program mirrors our plans for the

future, large-scale RCT. The population at risk will be screened for HTN because available health information systems do not allow us to obtain a sampling frame at the community level. To this end, sampling frames that comprise all adult community members will be obtained under the support of community collaborators. Based on the sampling frame, commune residents 50 years and older will be randomly selected for HTN screening. To minimize selection bias, enrollment of patients will proceed in a systematic and sequential manner until the full sample size has been obtained. At the initial trial visit, researchers will explain the study protocol to possible participants and obtain informed consent. Those screening positive for HTN and not willing to participate in the study will be referred for usual care.

### *Intervention Condition*

After obtaining informed consent, a trained community health worker will introduce the DVD to the patient, explaining its purpose and how to use the DVD. Participants will view each intervention DVD installment at their local health center first and then engage in a post-media interview and problem-solving session with a community health worker. After the clinic viewing, the patient will take the DVD home for subsequent review and sharing with family and friends. At three months after randomization, the second installment of the DVD will be delivered for home viewing. After the second viewing, a study visit will be scheduled for a “post-media” interview and re-measurement of BP by a trained community health worker.

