### *Comparison Condition*

Participants randomized to the comparison condition will receive DVDs with only didactic material about common non-communicable diseases (e.g. diabetes, heart disease, chronic lung disease—“Learn More”) but without HTN related stories. Otherwise, the treatment and study assessments for the intervention and comparison groups will be identical. The comparison group will receive usual medical care through the CHC.

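### The second DVD is delivered at the three-month date set for the BP outcome and the only dated follow-up, and the BP visit planned after it has no date

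*Protocol*

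**What the plan says.** Under Phase 1, Intervention Development: "The edited stories will be integrated into two interactive DVDs" and "Each DVD will have five stories on it and be about 30 minutes in length in total".

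Under Intervention Condition, the general rule is "Participants will view each intervention DVD installment at their local health center first", and then "After the clinic viewing, the patient will take the DVD home for subsequent review and sharing with family and friends". For the second DVD the text is different: "At three months after randomization, the second installment of the DVD will be delivered for home viewing". It continues "After the second viewing, a study visit will be scheduled for a" post-media interview and a new BP reading. No date or window is attached to that visit.

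The outcome dates are given elsewhere. The Summary (Study Design and Trial Outcomes) and Study Outcomes date the BP outcomes at three months after randomization. Data collection and management lists baseline and one follow-up visit, at 3 months. Study Outcomes also speaks of each follow-up visit, as if there were more than one, but no date later than three months appears anywhere. Missed visits are made up at home within 2 weeks.

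For the other arm, Comparison Condition says the DVDs hold didactic material "but without HTN related stories", and "Otherwise, the treatment and study assessments for the intervention and comparison groups will be identical". It gives neither the number of comparison DVDs nor their dates.

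**The concern.** An outcome meant to describe a two-part intervention should be measured once both parts have been given and had some time to act. Here the second part arrives on the date of the outcome.

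Two things are at stake. The first is engagement, a listed feasibility outcome. Data collection and management records it through viewing minutes, segments watched and sharing with family or friends. If those data are collected at month 3, there is essentially no home use of DVD 2 to record, although the trial is meant to guide revision of the intervention. The second is the BP comparison. It is exploratory, but it would be reported as the result of the storytelling intervention at three months, when half the stories have had little or no time to work.

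Delivery dates, visit dates and outcome dates are protocol content. The protocol states them and they collide, so this is not detail that a separate analysis plan could be expected to settle.

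**Working it through.** The protocol gives no figure for exposure to DVD 2, so there is none to reproduce. The check compares dates and amounts of content.

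**Inputs**
- Two DVDs, five stories and about 30 minutes each (Phase 1, Intervention Development).
- DVD 2 delivered at 3 months; BP visit after its viewing, undated (Intervention Condition).
- BP outcomes at 3 months (Summary; Study Outcomes); one dated follow-up visit, at 3 months (Data collection and management).
- Catch-up for missed visits: within 2 weeks (Study Outcomes).

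**Content on DVD 2 (intervention arm)**
- Stories: 2 × 5 = 10 in all, 5 of them on DVD 2 (50%).
- Minutes: 2 × about 30 = about 60 in all, about 30 of them on DVD 2.

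**Exposure at an on-time three-month visit**
- DVD 1 at home: 365.25 / 4 / 7 = about 13.0 weeks.
- DVD 2: 3 − 3 = 0 months.
- For a participant who misses the visit and is seen at home, at most 2 weeks, or 2 / (13 + 2) = 13% of follow-up. This applies only to those who miss the visit.

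**Possible readings of the schedule**

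| Reading | Exposure to DVD 2 when BP is taken | Date of BP |
|---|---|---|
| A. DVD 2 is first viewed at the health center at the month-3 visit, and BP is taken that day | All 10 stories seen, but 5 only that day; no home use of DVD 2 | Month 3 |
| B. DVD 2 is viewed at home, and one visit follows | All 10 stories seen, with short exposure | Later than month 3, interval not fixed |
| C. A month-3 visit and a further visit after DVD 2 | At month 3, 5 of 10 stories not yet seen | Month 3; further visit undated |

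Reading A follows the clinic-first rule but fits poorly with delivery for home viewing and a visit scheduled afterwards. Reading B follows the DVD 2 sentence but departs from the clinic-first rule and from the stated outcome date. Reading C rests on the reference to each follow-up visit.

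So A and C keep the date and lose exposure, while B gains some exposure and loses the date. Under B, the delay depends on when each participant watches the DVD and when local staff book the visit, so it can differ between participants and communes. Home viewing minutes for DVD 2 would then be counted over unequal periods.

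**The case against.** The best defence is that there is one follow-up visit, held at a nominal three months shortly after DVD 2 has been watched. BP is then taken after all 10 stories, and the defect is a loose date label. This is a fair reading of Intervention Condition, and staff calls every 2 weeks to encourage viewing make a long delay unlikely. It means one cannot say that the BP result reflects DVD 1 alone on every reading. What it leaves standing is a short exposure to DVD 2 and a delay that no sentence fixes.

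The engagement loss is also partial. Study Outcomes counts satisfaction and transportation as engagement, and both can be measured straight after one viewing. About 13 weeks of home use of DVD 1 is recorded on any reading. What is lost or left uneven is home viewing, segments and sharing for DVD 2.

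Third, BP is exploratory, and the Data Analysis Plan admits little ability to test effectiveness. That limits severity. It does not remove the conflict.

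A reader might go further and infer that the future trial would be sized wrongly by some factor, because Study Outcomes ties its sample size estimates to these findings. The documents do not support such a figure. They give no share of the full effect reached before DVD 2, Study Outcomes aims at differences that are meaningful rather than at the observed one, and the Data Analysis Plan names outcome variability, followed by the ICC, as what it will estimate for planning. A reader might also infer bias between arms. Treatment and assessments are stated to be otherwise the same in both arms, so that is not supported either.

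**Conclusion.** The conflict is certain from the text: delivery of DVD 2, the BP outcomes and the only dated follow-up visit share the three-month date, and the BP visit that follows DVD 2 has no date. Where DVD 2 is first viewed is also stated in two incompatible ways.

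The size is 5 of 10 stories (about 30 of 60 minutes) with little or no exposure at the outcome date, or else a BP and home-use assessment later than that date by an unfixed interval. Which of the two occurs depends on how the sites read Intervention Condition. That the comparison arm follows the same schedule is an inference from Comparison Condition, not something it states.

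The consequence is moderate. It concerns home-use engagement data for DVD 2 and the meaning of an exploratory BP comparison. Recruitment, retention, fidelity, variability and the ICC are not in question. Because the correction is cheap, it should be made before enrollment.

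**What to change.** Choose one of two schedules and apply it in both arms.

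1. **Earlier delivery.** Give DVD 2 well before month 3, for example at about week 6, which leaves about 13 − 6 = 7 weeks before the three-month visit. The outcome date stays as written. The cost is less time on DVD 1 alone: about 6 weeks instead of 13.
2. **Later assessment.** Keep delivery at month 3 and set one dated assessment after DVD 2 with a window (the 2-week catch-up rule is a ready model). Correct three months in the Summary, Data collection and management, and Study Outcomes. The cost is longer follow-up, some added retention burden and more support calls. As an illustration, an assessment three months after DVD 2 falls at month 3 + 3 = 6. That leaves 12 − 6 = 6 months of the trial phase in the Timeline for enrollment, and adds about 13 / 2, or roughly 6, two-weekly calls per participant (about 600 for 100 participants).

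Under either schedule, state whether DVD 2 is first viewed at the health center or at home, how many follow-up visits there are, which one supplies the BP outcome, and how many DVDs the comparison arm receives and when. Neither option adds participants.
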